## Methods and analysis

2

### Study design

2.1

This randomized, double-blind, controlled trial will be conducted at the Department of Rehabilitation Medicine, First Affiliated Hospital, Sun Yat-sen University, China. The trial will follow a blinded design in which assessors, therapists, and participants remain unaware of group assignments. Participants will be randomly assigned to one of two groups: (1) the Study Group receiving DLPFC-tDCS and (2) the Control Group receiving M1-tDCS. Assessments will be performed at baseline, 3 weeks, 6 months, and 12 months post-randomization, with the primary outcome evaluation occurring at 3 weeks. The study will be reported in accordance with CONSORT guidelines. The experimental flowchart is illustrated in Figure 1.

**Figure 1 fig1:**
[figure not shown]
The study flowchart diagram. DLPFC, dorsolateral prefrontal cortex; ES, erector spinae; fNIRS, functional near-infrared spectroscopy; MF, multifidus; M1, primary motor cortex; RA, rectus abdominis; sEMG, surface electromyography; TA, transversus abdominis; tDCS, transcranial direct current stimulation.

### Ethics

2.2

The study protocol has been approved by the Ethics Subcommittee of the First Affiliated Hospital of Sun Yat-sen University ([2023]710) and is registered in the Chinese Clinical Trial Registry (ChiCTR2300078887). Participants have the right to withdraw from the study at any time.

### Recruitment

2.3

Participants will be recruited through advertisements, outpatient clinics, and social media platforms. A designated research team member will conduct preliminary screening before study enrollment. The individual responsible for screening and assessments will remain blinded to the treatment group allocation. All eligible participants will receive detailed information about the study objectives and must provide written informed consent before participation. A screening log will be maintained to document non-recruited patients and reasons for exclusion.

### Participant retention

2.4

All study components and timelines will be clearly explained to participants during the eligibility screening process to minimize attrition. This approach aims to prevent data loss due to scheduling conflicts. Moreover, participants will receive appointment reminders *via* text messages. Treatment attendance will be documented for each intervention session to further support participant retention.

### Participants

2.5

#### Inclusion criteria

2.5.1

Clinically diagnosed with cLBP, intermittent or persistent pain below the 12th rib of the lower back;Chronic LBP lasting at least 12 weeks;Reported pain intensity of 4–7 on the Visual Analogue Scale (VAS) at least once in the past week;Age between 18 and 55 years;Right-handedness; andBoth male and female participants.

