#### Sample size

2.5.3

Based on the following formula and our preliminary experimental results of the primary outcome measures (VAS), with a significance level of *α* = 0.05, test power (1-*β*) = 0.9, a mean difference of 1.15, and a variance index of 1.48, it was determined that 20 participants per group are required. To account for an estimated attrition rate of 120%, a total of 48 cLBP participants will be recruited. To compare the effects after the intervention of the two groups, twenty-four right-handed healthy individuals with no history of cLBP were recruited.

$$N={\left[\frac{(t_{\alpha ∕2}+t_{\beta })S}{\delta }\right]}^{2}$$

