##### Pain intensity

2.10.1.1

Pain intensity will be assessed using the VAS, which ranges from 0 to 10 cm, where “0 cm” indicates no pain and “10 cm” represents unbearable pain. Moreover, the Short-Form McGill Pain Questionnaire (SFMPQ) will be used to evaluate each participant’s pain experience (Strand et al., 2008). The SFMPQ consists of 15 items divided into two categories: affective scores (4 items) and sensory scores (11 items). Each item is rated on an intensity scale from 0 to 3 (0 = none, 1 = mild, 2 = moderate, 3 = severe). Pain assessments will be conducted at all time points, including baseline, 3 weeks, 6 months, and 12 months post-randomization. Meanwhile, during the follow-up period, we will record whether the patients are using painkillers or other treatments.

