##### Disability

2.10.1.2

Disability associated with cLBP will be measured using the Oswestry Disability Index (ODI), a validated tool consisting of 10 questions, each with 6 response options scored from 0 to 5. This index evaluates functional impairment in cLBP by incorporating pain and physical activity measures. Based on the total score, disability is categorized as bed-ridden (81–100%), crippled (61–80%), severe disability (41–60%), moderate disability (21–40%), or minimal disability (0–20%) (Martí-Salvador et al., 2018). Participants will be instructed to complete the questionnaire based on their condition on the day of assessment.

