##### Mental health

2.10.1.3

Mental health will be assessed using the short version of the Hamilton Depression Scale (HDS) and the Hamilton Anxiety Scale (HAMA). The HDS consists of three subscales, each comprising seven items, designed to evaluate anxiety, depression, and stress over the previous week (Kaptan et al., 2012). Responses are rated on a scale from 0 to 3 (fully disagree to fully agree), with total scores indicating symptom severity: a score of 13 or higher suggests depressive symptoms, 14–27 indicates mild depression, 28–41 reflects moderate depression, and scores of 42–53 suggest high level depression. The HAMA is primarily used to evaluate the severity of anxiety symptoms in individuals with neurosis and other conditions. It evaluates 14 aspects of anxiety, including mood, depressive mood, cognitive function, insomnia, fear, tension, somatic anxiety, reproductive and urinary symptoms, gastrointestinal and digestive symptoms, respiratory symptoms, cardiovascular symptoms, sensory symptoms, and behavioral responses during social interactions (Yin et al., 2023).

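### The entry pain rule allows a wide spread of baseline VAS and the outcome VAS has no stated reference period, yet baseline VAS is analysed as an outcome time point, not used as a covariate

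*Protocol article*

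**What the plan says.** Section 2.5.1 (Inclusion criteria) of the protocol article accepts "intermittent or persistent pain below the 12th rib of the lower back" and requires "Reported pain intensity of 4–7 on the Visual Analogue Scale (VAS) at least once in the past week". Neither the inclusion nor the exclusion list sets a minimum VAS at the baseline assessment.

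Section 2.10.1.1 (Pain intensity) defines the outcome as follows: "Pain intensity will be assessed using the VAS, which ranges from 0 to 10 cm". It adds the two end anchors and the schedule: "Pain assessments will be conducted at all time points, including baseline, 3 weeks, 6 months, and 12 months post-randomization". It does not say whether the rating is of current, average or worst pain, or over what period. Two other primary instruments do have a window. For the ODI (2.10.1.2) participants "complete the questionnaire based on their condition on the day of assessment", and the depression scale (2.10.1.3) is "designed to evaluate anxiety, depression, and stress over the previous week".

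Section 2.5.3 (Sample size) sizes the trial on VAS, using preliminary results with "a mean difference of 1.15, and a variance index of 1.48". Section 2.1 (Study design) places the primary evaluation at 3 weeks, and section 2.9 (Data collection) has baseline data gathered before randomisation. Section 2.11.1 (Statistical analysis) names a repeated-measures ANOVA with two groups and four time points for primary and secondary outcomes, so baseline is one of the four. It mentions no baseline covariate.

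**The concern.** The entry rule looks as if it fixes the baseline pain level, but it does not. One reading in the range at any time in the week is enough, so it does not determine what the participant reports at the baseline visit. Someone with intermittent pain who had one qualifying reading some days earlier could report little or no pain at baseline if the outcome VAS asks about pain now. By the letter of the rule, someone usually above 7 who had one reading of 7 also qualifies.

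Two things are at stake, both about precision and sensitivity. Participants who start near the floor have little room to improve, which would pull the mean between-group difference down. A wide spread of baseline values also adds variability to the 3-week values, and an analysis that does not condition on baseline leaves that variability in the error term. In a trial of 24 per arm this matters.

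**Working it through.** **Inputs from the protocol article.** Mean difference δ = 1.15; S = 1.48; two-sided α = 0.05 (the formula uses α/2); planned power 0.90; 20 per group before attrition and 24 per group recruited (2.5.3).

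**Inputs that are assumptions.** 1.48 is the per-arm SD of VAS at 3 weeks. The article calls it a variance index but enters it in the formula as S. The correlation r between baseline and 3-week VAS is not given; the range 0.3 to 0.6 is used.

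**Step 1: reproduce the plan's figure.** The plan's formula is N = [(t for α/2 + t for β) × S / δ]².
- With t quantiles on 19 degrees of freedom: [(2.093 + 1.328) × 1.48 / 1.15]² = 19.4, rounded up to 20. This matches the article.
- Reading 1.48 as a variance (SD = √1.48 = 1.217) gives 14 in the same formula, so the stated 20 fits the SD reading.
- 20 × 1.2 = 24 per group, 48 in total.

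**Step 2: power of an unadjusted comparison of 3-week VAS.** Noncentral t, noncentrality = (δ / SD) × √(n/2).
- n = 24: (1.15 / 1.48) × √12 = 2.69 on 46 degrees of freedom; power 75%.
- n = 20: (1.15 / 1.48) × √10 = 2.46 on 38 degrees of freedom; power 67%.

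The gap between these values and the planned 90% comes from the one-sample form of the formula applied to a two-group comparison. That is a separate matter; 75% is used here only as the reference for the gain.

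**Step 3: the same comparison with baseline VAS as covariate.** Residual SD = 1.48 × √(1 − r²), with one degree of freedom spent on the covariate.

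| r | Residual SD | Power, 24 per arm | Power, 20 per arm |
|---|---|---|---|
| 0.3 | 1.41 | 79% | 71% |
| 0.4 | 1.36 | 82% | 74% |
| 0.5 | 1.28 | 86% | 79% |
| 0.6 | 1.18 | 91% | 85% |

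**Step 4: what treating baseline as a time point amounts to.** With baseline among the repeated measures, the group-by-time contrast between baseline and 3 weeks compares changes from baseline. The SD of a change is 1.48 × √[2(1 − r)], assuming equal SDs at the two visits.
- r = 0.3: SD 1.75, power 61% at 24 per arm.
- r = 0.6: SD 1.32, power 84% at 24 per arm.

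At each r, adjusting for baseline has a smaller SD than either the change or the raw 3-week value.

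**Step 5: what cannot be computed.** If a share of participants sat at the floor and contributed no difference, the mean difference would shrink in proportion to that share. The article gives neither the share nor the distribution of baseline VAS, so no figure for this loss is offered.

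**The case against.** The strongest reply is that an article condenses a fuller protocol, and that the exact VAS question belongs on the case report form. The article also states no window for the McGill questionnaire or the anxiety scale, which fits condensation. This stands: the missing reference period alone would be detail left elsewhere, and the article nowhere says that the outcome VAS is a current rating. If the form asks for worst pain in the past week, a participant who entered on one recent qualifying reading would not score near zero.

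A reader might go further and infer that participants with no pain on the visit day make the planned 1.15 unattainable. The documents do not support that. The 1.15 is a difference between group means, not a change that each person must show, and the preliminary results may have come from a similar population with the same VAS. Some dilution and day-to-day noise may then already be in the 1.15 and 1.48. A reader might also expect a large gain from asking about the past week's average. One recalled rating is not the mean of seven separate daily readings, so no such gain can be claimed.

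It is also fair to say that entry and measurement rules are the same in both arms, so no bias arises, and that admitting intermittent pain is a deliberate eligibility choice. None of this answers the analysis point: baseline VAS is already collected before randomisation, and the stated model does not use it as a covariate.

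**Conclusion.** The point holds as one of precision, not of validity. The entry rule leaves baseline VAS loosely bounded. If the outcome is a current rating, floor effects are possible, of a size that the documents do not reveal. The part that can be sized is the gain from adjusting the 3-week comparison for baseline: from 75% to about 79% to 91% power at 24 per arm, or from 67% to about 71% to 85% at 20 per arm.

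These figures assume a per-arm SD of 1.48, a true difference of 1.15 and a correlation of 0.3 to 0.6. A lower correlation gives a smaller gain. If 1.48 were a variance, the unadjusted power at 24 per arm would already be about 91% (normal approximation) and the gain would be correspondingly smaller. Adjustment does not restore a difference lost to floor effects; it only removes variation that baseline explains.

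**What to change.** 1. In section 2.11.1, specify the primary 3-week VAS comparison as an ANCOVA with baseline VAS as covariate, or as a mixed model for the post-randomisation visits with baseline VAS as covariate and the group difference at 3 weeks as the primary contrast. Baseline then leaves the list of outcome time points. **Cost:** a change of wording and one degree of freedom; no new data.

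2. In section 2.10.1.1 and on the case report form, state one VAS reference period and ask the question identically at screening, baseline, 3 weeks, 6 months and 12 months. Choose the period used in the preliminary work behind 1.15 and 1.48, so that the sizing inputs still describe the outcome. A stable question should also help the baseline-to-3-week correlation on which the gain in item 1 depends. **Cost:** wording and assessor instruction.

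3. The investigators should reconcile the entry criterion in 2.5.1 with that outcome definition. Which pain range and pattern to admit is their decision; a tighter rule would change who is eligible and could slow recruitment.

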#### Exclusion criteria

2.5.2

Diagnosed or suspected serious spinal conditions (e.g., tumors, fractures, rheumatologic or inflammatory disorders, spinal infections);Presence of nerve root impairment;History of spinal surgery, including procedures outside the lumbar region or planned spinal surgery;Pain related to pregnancy or structural deformities (e.g., scoliosis);Current pregnancy;Comorbid conditions that could limit participation in exercise programs, such as hypertension or cardiorespiratory disease;Contraindications to tDCS, including the presence of a pacemaker, artificial metal heart valve, aneurysm clips (except titanium alloy), or other metal implants;Ongoing physical therapy or participation in structured exercise programs;Mental illness;Current use of nonsteroidal anti-inflammatory drugs (NSAIDs) or planned initiation of NSAID therapy during the trial; andInability to tolerate the experimental procedures.

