**Methods:**

This study is a randomized, double-blind, controlled trial. Forty-eight individuals aged 20 to 55 years with cLBP will be randomly assigned to receive either (1) a 3-week DLPFC-tDCS intervention (*n* = 24) or (2) a 3-week M1-tDCS intervention (*n* = 24), administered four times per week for a total of 12 sessions. Clinical outcomes will be assessed at baseline, 3 weeks, and 6 and 12 months after randomization. Primary outcomes include pain intensity, disability, and scores on the Hamilton Depression and Hamilton Anxiety scales. Secondary outcomes include surface electromyography characteristics of trunk muscles, oxygenated and deoxygenated hemoglobin concentrations in the M1 and DLPFC, and functional connectivity between these two brain regions. These outcomes will be evaluated before and after the intervention. Effect sizes and a mixed-model repeated measures analysis of variance (2 groups × 4 time points) will be calculated.

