This study primarily aims to assess the role of M1-DLPFC functional connectivity in regulating trunk muscle synergy patterns in cLBP patients. The primary hypothesis proposes that abnormal trunk muscle synergy in cLBP is associated with reduced M1-DLPFC functional connectivity. The secondary objective is to evaluate the effects of M1-tDCS and DLPFC-tDCS post-intervention and at follow-up in terms of (1) pain, (2) disability, (3) mental health, (4) surface electromyography characteristics of trunk muscles, and (5) the concentration of oxygenated and deoxygenated hemoglobin in the cerebral cortex of M1 and DLPFC. The secondary hypothesis is that DLPFC-tDCS is more effective than M1-tDCS in increasing M1-DLPFC functional connectivity and improving symptoms of depression and anxiety.

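### Depression and anxiety scores are primary outcomes in a cohort that excludes undefined mental illness and needs no mood symptoms at entry, so the mood comparison may lose sensitivity by an unknown amount.

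*Protocol article*

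**What the plan says.** All places are in the protocol article.

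- **Eligibility.** Section 2.5.2 lists two adjacent exclusions, printed as "Mental illness;Current use of nonsteroidal anti-inflammatory drugs (NSAIDs". The first is the one at issue. It comes with no diagnosis list, severity or screening instrument. Section 2.5.1 sets a symptom level for pain, "Reported pain intensity of 4–7 on the Visual Analogue Scale (VAS) at least once in the past week", and none for depression or anxiety.
- **Outcome status.** The abstract states: "Primary outcomes include pain intensity, disability, and scores on the Hamilton Depression and Hamilton Anxiety scales". Section 2.10.1.3 describes both mood scales under the primary-outcome heading, and section 2.1 places the primary evaluation at 3 weeks.
- **Hypothesis.** The Introduction gives, as the secondary hypothesis, that "DLPFC-tDCS is more effective than M1-tDCS in increasing M1-DLPFC functional connectivity and improving symptoms of depression and anxiety".
- **Depression scale.** Section 2.10.1.3 says "The HDS consists of three subscales, each comprising seven items" and "Responses are rated on a scale from 0 to 3 (fully disagree to fully agree", with the reading that "a score of 13 or higher suggests depressive symptoms, 14–27 indicates mild depression". It gives no cut-off for the anxiety scale.
- **Sample size and analysis.** Section 2.5.3 sizes the trial on VAS alone. Section 2.11.1 plans a 2 × 4 repeated-measures ANOVA for all outcomes.

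**The concern.** For pain, the plan makes sure that participants enter with something to reduce. For mood, which has the same primary status, it requires no symptoms and excludes a group that, on a plain reading, includes people with depressive or anxiety disorders. Mood is not incidental here: the Introduction argues for the DLPFC target partly because its stimulation also acts on connections related to cognition and emotion.

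What is at stake is how the mood result will be read. If the cohort has few symptoms, a difference between arms is harder to detect. A null finding on two primary outcomes could then be reported as DLPFC-tDCS having no advantage for depression or anxiety, in a population from which people with those conditions may have been removed. These are choices of eligibility, outcome and hypothesis, all printed in the article, and no analysis plan can undo them.

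**Working it through.** **1. Pain and mood side by side**

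| | Pain (VAS) | Depression and anxiety scores |
|---|---|---|
| Entry level (2.5.1) | 4–7 | none |
| Related exclusion (2.5.2) | no upper or lower limit beyond the entry level | mental illness, undefined |
| Outcome status (abstract, 2.10.1) | primary | primary |
| Place in the Introduction | secondary objective | secondary objective and secondary hypothesis |
| Input to sample size (2.5.3) | difference 1.15, variance index 1.48 | none |

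**2. The plan's own figure**

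The printed formula is N = [(t_α/2 + t_β)S/δ]², with S = 1.48, δ = 1.15, α = 0.05 two-sided and power 0.90.
- With normal quantiles: [(1.960 + 1.282) × 1.48/1.15]² = 17.4.
- With t quantiles iterated on N − 1 degrees of freedom: 19.4, so 20 per group as stated.
- 20 × 1.2 = 24 per group, 48 in total.

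The figure reproduces. It uses VAS only, so nothing in the document sizes the mood comparison.

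**3. Room on the depression scale as described**

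3 × 7 = 21 items, and 21 × 3 = 63 points at most. If the exclusion removes everyone from mild depression (14) upwards, eligible scores are 0–13, and 13/63 = 21% of the range. If it removes only severe disorder, higher scores stay eligible. The anxiety scale cannot be treated in this way, because no item range or cut-off is given for it.

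**4. Illustration of the loss (assumptions, not estimates)**

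No mean, SD or expected effect is given for either mood scale. Borrow the VAS effect, reading 1.48 as an SD: 1.15/1.48 = 0.777. Take 20 per arm and a two-sided 5% test.

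*Dilution.* A share f cannot change and the SD is unaffected. Power ≈ Φ[(1 − f) × 0.777 × √(20/2) − 1.96].
- f = 0: Φ(2.457 − 1.96) = 69%
- f = 0.25: Φ(1.843 − 1.96) = 45%
- f = 0.50: Φ(1.229 − 1.96) = 23%
- f = 0.75: Φ(0.614 − 1.96) = 9%

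*Censoring.* Normal 3-week scores with SD 1, the DLPFC arm 0.777 lower, values below the floor set to the floor, t-test, 20,000 simulated trials.

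| Control arm at floor | 2% | 16% | 31% | 50% | 69% |
|---|---|---|---|---|---|
| Power | 66% | 62% | 56% | 45% | 29% |

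The formula is a normal approximation. The exact t calculation at f = 0 gives 67%, so 66% with 2% at the floor is almost no loss. The two models define the affected share differently, but at one half they give 23% and 45%. The answer is set by the model and by a baseline distribution that nobody has stated.

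The starting value is 69% and not 90% because the printed formula lacks the factor 2 for two independent groups. That is a separate matter.

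**The case against.** The strongest reply is that the exclusion names an illness and not a score. People with at least 12 weeks of back pain can have distress short of a diagnosis, and nothing in the eligibility criteria removes them. Someone who enters with 10–12 points on the depression scale is below the protocol's symptom line of 13 and can still fall by 10–12 points. How mental illness is defined and screened may stand in the full protocol, which a journal article condenses. The exclusion may also have a safety or confounding reason. All of this stands, and the missing definition alone is not held against the plan.

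A reader might go further and infer that many participants will start near the floor, and that the trial cannot show a mood effect. The documents do not support this. They give no baseline distribution, scores below the line can fall, and the power figures rest on a borrowed effect and an assumed affected share. Nor do they give data to show that skewed scores would invalidate the planned ANOVA.

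It can also be said that the secondary label does not single mood out, since the Introduction puts pain and disability under the secondary objective too. That is fair. The clearer contrast is that pain has an entry level and drives the sample size, and mood has neither.

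The reply does not explain why scores with no entry level, no sizing and a potentially broad exclusion should carry primary status.

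**Conclusion.** The point holds as an inconsistency between eligibility, outcome status and hypothesis. Depending on how broadly the exclusion is applied, the mood comparison may lose sensitivity. Under the borrowed effect of 0.777, the loss runs from almost none to a fall from about 69% to somewhere between 9% and 29%. That range illustrates assumptions and is not an estimate for this trial.

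The firm conclusion concerns interpretation. A null mood result would apply to cLBP patients without diagnosed mental illness, and would not show lack of efficacy in people with depression or anxiety. The point calls for a modest correction and does not threaten the trial as a whole.

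**What to change.** - Reconcile the abstract, the Introduction and sections 2.5.2, 2.5.3 and 2.10.1.3 by listing the depression and anxiety scores as secondary outcomes. The exclusion can stay as it is.
- Compare the 3-week mood scores between arms with the baseline score as covariate. This targets the primary time point directly and takes account of where each participant started, which the 2 × 4 ANOVA does less well.
- Describe the mood result as applying to cLBP patients without diagnosed mental illness.
- If a loss of power is reported, label it as an illustration and state its assumptions.

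A separate analysis of participants above the symptom line is not advised. A broad exclusion could leave that subset nearly empty, and the anxiety scale has no line to apply. Even with an assumed standardised effect of 0.8, power would be only 47% with 12 per arm and 24% with 6 per arm.

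The cost is a few lines of text and one change of model. The downside is that mood loses primary status and the mood claim becomes narrower.
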